
##### Multisensory Integration

Four web-based perceptual tasks will be performed: (1) the audiovisual response time (RT) task, (2) the sound-induced flash illusion (SIFI), (3) the simultaneity judgment (SJ) task, and (4) the temporal-order judgment (TOJ) task. The audiovisual RT, SJ, SIFI, and TOJ tasks have been specifically designed for web-based data collection. These tasks will be used to obtain various measures of sensory integration, including RT (to assess RT differences between uni- and multisensory cues), temporal binding window (TBW; the window of time during which stimuli from different modalities are bound together), and susceptibility to the SIFI (where the observer misperceives the number of visual flashes owing to the presentation of 2 auditory beeps in close temporal proximity).

The participants will be asked to sit in a quiet, dark room while directly facing their computing device, which will be placed at arm’s length. The visual stimuli will be presented in the form of white circles, subtending approximately 2° of visual angle. The visual stimuli will appear approximately 8° below the fixation cross (visual angle=1.5°), which will appear at the center of the screen and will remain on display throughout the trial for 16 ms. The participants will be asked to fixate on the fixation cross throughout the duration of each task. Auditory stimuli will be presented in the form of beeps (16 ms) through speakers that are either connected to the participant’s device or through external speakers placed beside the screen. To reduce temporal predictability, each trial will begin with the stimulus being presented after a delay of 1000 to 3000 ms. A computer keyboard will be used by the participants to input their responses for each trial; a response from the participant will initiate the next trial for each task. The participants will complete the RT, SJ, SIFI, and TOJ tasks in a randomized order where they will be explicitly asked to respond as accurately as possible as opposed to responding quickly for the SJ, SIFI, and TOJ tasks while responding as quickly as possible for the RT task. The participants will be presented with practice trials before the commencement of each of the experimental tasks. The following stimulus onset asynchronies (SOAs; the amount of time between the start of one stimulus, S1, and the start of another stimulus, S2) will be used for the multimodal conditions in the SJ, TOJ, and SIFI tasks: 0 ms, −70 to +70 ms, −150 to +150 ms, and −230 to +230 ms; here, *+* indicates vision-led trials, whereas − indicates auditory-led trials.

For the SIFI task, there will be 3 conditions: vision-only, auditory-only, and audiovisual. In the vision-only block, 2 flashes will be presented, and the participant’s task will be to indicate the number of flashes they saw. In the auditory-only block, 2 beeps will be presented, and the participants will be asked to indicate the number of beeps they heard. There will be 30 trials in each of the unimodal conditions (SOAs: 70 ms, 150 ms, and 230 ms). The audiovisual trials will consist of 2 control conditions (1 beep and 1 flash and 2 beeps and 2 flashes) as well as the illusion condition (2 beeps and 1 flash). In the audiovisual control conditions, the auditory and visual stimuli will be presented simultaneously. In the 2 beeps and 1 flash (illusory condition) auditory-led trials, the auditory stimulus will be presented first, after which the auditory and visual stimuli will be presented simultaneously following a variable SOA. In the 2 beeps and 1 flash vision-led trials, the first auditory stimulus will be accompanied by a visual stimulus, and the second auditory beep will follow a variable SOA. The 3 audiovisual conditions will be randomly presented within the testing block to avoid response bias. The participants will be asked to fixate on the fixation cross for the duration of the task, report the number of flashes seen, and ignore the auditory stimuli. All conditions will be repeated 10 times for a total of 100 trials (including 10 repetitions for 0 SOAs, where a single beep and flash will be presented simultaneously). In total, 160 trials, as well as additional practice trials, will be presented for all 3 conditions (vision-only, auditory-only, and audiovisual). This task will take approximately 5 to 10 minutes to complete.

For the SJ task, the participants will be instructed to report, using the number *1* and *2* keys on their keyboard, whether they perceived the auditory and visual stimuli as occurring simultaneously (number *1* key) or not (number *2* key). A total of 10 trials will be presented in a randomized order for each SOA, and 6 practice trials will also be presented for a total of 76 trials. This task will take approximately 5 to 10 minutes to complete. The experimental design of the TOJ task will be identical to that of the SJ task with the exception of the task instructions. In this case, the participants will be asked to report, using the number *1* and *2* keys on their keyboard, whether they perceived the visual (number *1* key) or auditory (number *2* key) stimulus as appearing first.

For the RT task, the participants will be told that they will see a flash of light, hear a beep, or a combination of the 2, and they will be instructed to press the response button (space bar key) as soon as they detect any of the 3 experimental conditions. Each condition will be presented 50 times in a random order with 6 practice trials for a total of 156 trials. However, if a participant responds too quickly (<100 ms) or takes longer than 3 seconds to respond to a trial, that trial will be repeated. This task will take approximately 5 to 10 minutes to complete.

Both the multisensory integration and modified flanker tasks will be designed using PsychoPy (Open Science Tools Ltd) and distributed on the web using Pavlovia (Open Science Tools Ltd), wherein the participants will be provided with URLs to access the tasks. All instructions will be embedded within the tasks and will not require the presence of a researcher to be completed. However, a researcher will join the participants for the duration of the first session of these tasks to ensure that all inquiries and technical difficulties are resolved as soon as they arise. Furthermore, 1 to 2 members of the research team will check in with the participants every 2 weeks to answer any questions and ensure that they are following the protocol.

##### Physical Activity, Exercise Self-efficacy, and Mood

The Physical Activity Scale for the Elderly (PASE) [76] and RPE will be used to assess the participants’ physical activity behavior. In the PASE, the participants will be asked to self-report the frequency with which they take part in leisure, household, and occupational activities (eg, outdoor walking; light, moderate, and strenuous sports and recreation; and muscle strengthening) by indicating never, 1 to 2 days per week (seldom), 3 to 4 days per week (sometimes), or 5 to 7 days per week (often). Activity duration will be indicated as <1 hour, between 1 and 2 hours, 2 to 4 hours, or >4 hours. RPE will be assessed through a paper-based pictorial omnibus scale wherein the participants will be asked to indicate how physically exhausting the VR exergaming was using a 10-point Likert scale ranging from *extremely easy* to *extremely hard* [64].

Mood will be assessed using the Physical Activity Affect Scale (PAAS) [77]. Affective states are thought to be highly influenced by exercise, thus leading to the development of the PAAS as a concise affect measurement tool [77-79]. The PAAS has 12 items, which can be further broken down into 4 subdomains, each further broken down into 3 mood states: positive affect (upbeat, energetic, and enthusiastic), negative affect (miserable, discouraged, and crummy), physical exhaustion (tired, worn-out, and fatigued), and tranquility (calm, peaceful, and relaxed). Exercise self-efficacy will be assessed using the Bandura exercise self-efficacy scale, which is a predictor of the adoption and maintenance of exercise behavior [80]. The Bandura scale includes 9 statements, and the participants will be asked to rank each statement from 1 to 4 indicating their belief in their ability to continue exercising in the future.

##### Automatic Data Logging System

*Seas The Day* includes a data logging system that allows for the capture of data related to game events and interactions inside the virtual environment during gameplay. In every session, the data logging system locally records data using a time series at 30 Hz combining game events, scores, achievements, and kinematic information from the VR equipment (controllers and headset). The data logging system records the following information: (1) tai chi (time to complete the activity and interactions with animals [when players were looking at them]), (2) rowing (boat speed, distance traveled, number of strokes [right or left], boat collisions, and interactions with the dolphin), and (3) fishing (number of fish caught, pulling out the fishing rod [number of repetitions], and RT after the fish is hooked). The kinematic information is captured through the inertial motor units embedded in the 2 VR controllers and the headset, recording 3-axis accelerometer information of the 3 points (head and right and left hand). Both game variables and kinematic information are locally stored in the headset and compressed in files of 15 MB.

### Statistical Analysis Plan

#### Sample Size

Given that the primary purpose of the study is to assess the feasibility and usability of at-home VR exergaming over a 6-week period, no formal sample size calculation will be performed [81]. However, to explore data collection processes and also inform sample size calculations for a larger trial, the study will aim to recruit at least 12 participants for both the experimental and control groups [82].

#### Feasibility Analysis

Feasibility will be assessed through the recruitment rate (number of participants divided by the total number of potentially eligible participants), attrition rate (percentage of participants who did not complete the study), and adherence rate (number of completed exergaming or reading sessions divided by the total number of potential exergaming or reading sessions). Appropriate qualitative analyses will be carried out to provide further details regarding the feasibility, usability, and acceptability of the VR exergame as well as the study protocol. The focus group or semistructured interview script includes open-ended questions (Multimedia Appendix 3). These questions were refined through pretesting with a volunteer group of older adults (n=5) to ensure clarity and prompt discussion relevant to the issues of immediate interest [61]. Using a focus group allows the participants to exchange viewpoints and engage in conversations with peers to express general agreement or disagreement on various aspects of our study [83,84]. Individual interviews, by contrast, allow for a deeper understanding of the participants’ experiences, beliefs, and attitudes through direct, one-on-one engagement [85]. Both methods will be considered in our study; however, deciding on whether to participate in a focus group or a one-on-one interview (or both) will be based on the participants’ preferences and what would be the most feasible for them.

Focus groups or interviews will be digitally recorded (via videoconferencing platforms) and transcribed verbatim. All qualitative data (ie, focus groups or interviews, self-reported physical or emotional discomfort, and the participants’ informal notes and reports) will be organized and coded using NVivo (version 12; QSR International) [86]. Inductive and deductive thematic analyses (informed by the feasibility, usability, and acceptability objectives of the study) will be performed after line-by-line coding to identify key topics and patterns of meaning across the data [87-89]. Open coding and axial coding will be conducted by multiple researchers independently to enhance the rigor of data analysis [89-91]. Researchers will use reflexive memos during the coding process to reflect on the emerging themes and patterns [87,92,93]. To create a robust codebook, researchers will regularly meet to resolve any coding challenges or discrepancies. The codebook will be refined by discussing the coding scheme (as different key topics emerge) and merging or deleting overlapping codes. After a consensus is reached, the codebook will include definitions and examples of each code, and the coding process will continue until data saturation (ie, no new data and no new themes are observed) [94,95]. Codes will then be categorized to detect overarching themes as well as subcategories to support themes [87].

#### Outcome Analyses

Descriptive statistics will be calculated for all demographic and baseline characteristics of the participants and presented as means and SDs or percentages (n), as appropriate. Assumptions underlying the statistical procedures will be checked, and corrective procedures will be used if necessary. Statistical analyses will be performed in R Studio (R Foundation for Statistical Computing) and SPSS (IBM Corporation). Data from the cognitive and perceptual tasks will be assessed for normality using *Q*-*Q* plots, the Shapiro-Wilk test, and histograms. Homogeneity of variance will also be tested using the Mauchly sphericity test, and Greenhouse-Geisser corrections will be applied if necessary. Potential deviations from a normal distribution will be identified in all cognitive and perceptual task data sets, and log transformations will be applied to the raw skewed data if deemed necessary to transform the data into a normal distribution. Paired and independent 2-tailed *t* tests will be used to compare the baseline, follow-up, and acute scores. Repeated-measure and mixed ANOVAs will be used to analyze before and after intervention data (exergaming or reading for 6 weeks) as well as acute data (before and after 1 bout of exergaming or reading) to understand changes by time (before and after), group (control vs experimental), and day (eg, weeks 2, 4, and 6 for SIFI) to compare baseline, follow-up, and acute scores.

#### Executive Function

Cognitive data from the OTMT (completion time [seconds] for parts A and B separately) and VF (the number of unique animal names) will be analyzed for within-participant and between-participant variables. For the modified flanker task, the participants’ mean RT and proportion error (1-accuracy) for each block of flanker responses will be obtained and further separated by congruence (congruent, incongruent, and neutral). Incorrect responses, responses that occurred 1000 ms after stimulus onset, and double responses for a single stimulus will be considered as errors and excluded from the analysis. The rate of no response and gender will be included as covariates.

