##### Executive Function

Measures of executive function will consist of a web-based modified flanker task, the Oral Trail Making Test (OTMT) parts A and B, and a verbal fluency (VF) test (animal naming). The modified flanker task includes a set of response inhibition tests to assess the ability of the participants to suppress responses that are inappropriate in a particular context [68,69]. In total, 3 types of stimuli—incongruent, congruent, and neutral—will be represented by arrowheads. In all sessions, the participants will be asked to complete 4 blocks: 1 practice block consisting of 30 mixed stimuli (10 experiments per flanker arrow type) to help familiarize the participants with the task, 2 blocks consisting of 100 trials (20 incongruent and 80 congruent flanker arrows [70]), and 1 block consisting of 100 trials (all neutral flanker arrows). The display duration of the flanker arrows will be 150 ms, and the intertrial interval duration (from a + sign to the next) will be 1500 ms (−100 to +100 ms). The participants will be asked to sit in a quiet room while directly facing their computing device. They will be instructed to keep their index fingers on the right and left arrow keys of their computer keyboard (to indicate the direction of the flanking arrow), look at a small white fixation cross in the middle of a black screen where the target stimuli will appear, and respond as quickly and accurately as possible. The task will take approximately 10 to 15 minutes to complete, and the participants will be able to take a break in between blocks if they wish. The OTMT is a neuropsychological test and can reflect a wide variety of cognitive processes [71-73]. The test consists of 2 conditions: condition A, in which the participants are instructed to count from 1 to 25, and condition B, in which the participants are instructed to count in an alternating numeric and alphabetic sequence (ie, 1-A-2-B). The goal of the test is for the participant to finish both parts as quickly as possible, and the time taken to complete the test will be used as the primary performance metric. The OTMT takes approximately 2 to 5 minutes to complete. VF is a widely used test of executive function in which the participants will be given 60 seconds to produce as many unique words as possible within a semantic category (ie, names of animals) [74,75]. The number of unique words will be the participant’s score on this task. Both the OTMT and VF will be administered in an oral format via phone or an audio- and videoconferencing platform with the guidance of a trained researcher.

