##### RT Task

Data trimming procedures will not be applied [99,102]; however, responses faster than 100 ms and slower than 1500 ms will be set to infinity rather than excluded [99,103] where this method of data trimming was used. The mean RT for each modality (auditory, visual, or audiovisual) before and after the experimental and control conditions will be calculated individually for each participant, and appropriate analyses will be conducted to determine the impact of time and modality. Acute data (before and after exergaming or reading) will also be analyzed as described previously.

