#### Gameplay Metrics

Game metrics captured by the data logging system will be analyzed session by session, and specific metrics associated with game performance, errors, and RT will be extracted from the described variables. First, changes in SD units for each session will be determined for 3 main variables denoting game performance on each game activity: time to complete the tai chi condition, distance traveled during the rowing condition, and the number of fish caught in the fishing condition. The number of collisions will be identified as a potential variable to quantify errors during rowing. RT will be computed in the fishing condition, where the time taken by players to pull out the fishing rod after feeling the fish being hooked (controllers vibrating) will be extracted from the data files. Time will then be filtered, and values outside the 100 to 1000 ms range will be discarded [104]. All numerical data will be presented as means and SDs.

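### The flanker exclusion rule has a slow limit but no fast one, although the protocol's two other trial-level response-time measures treat responses under 100 ms as invalid

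*Protocol article*

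**What the plan says.** The flanker rule is in the Executive Function section of the Statistical Analysis Plan: "Incorrect responses, responses that occurred 1000 ms after stimulus onset, and double responses for a single stimulus will be considered as errors and excluded". The outcomes are given just before it: "mean RT and proportion error (1-accuracy) for each block of flanker responses will be obtained", further split by congruence. The same section makes the rate of no response a covariate. The task description under Outcomes and Measures, Executive Function, adds no lower limit. It sets out "2 blocks consisting of 100 trials (20 incongruent and 80 congruent flanker arrows") and "1 block consisting of 100 trials (all neutral flanker arrows"), paced so that the "intertrial interval duration (from a + sign to the next) will be 1500 ms", with a jitter of 100 ms either way.

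Two other measures are built from single-trial response times, and each has a 100 ms floor:

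- Audiovisual RT task, at data collection (Multisensory Integration): "if a participant responds too quickly (<100 ms) or takes longer than 3 seconds to respond to a trial, that trial will be repeated".
- Audiovisual RT task, at analysis (RT Task): "responses faster than 100 ms and slower than 1500 ms will be set to infinity rather than excluded".
- Fishing-game RT (Gameplay Metrics): "values outside the 100 to 1000 ms range will be discarded".

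The Exploratory Analysis section plans correlations of RT between the game metrics and the flanker and RT tasks.

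**The concern.** A key press within 100 ms of the stimulus is, by the standard the protocol applies to its other two RT measures, not a response to that stimulus. The flanker rule does not remove it. With two keys, a blind press is right about half the time. A correct one meets none of the listed exclusions and enters mean RT as a very short time. A wrong one counts as an error. The double-response clause catches an early press only if a second press follows it.

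The flanker task is plausibly exposed to anticipation. Its onset varies within a 200 ms range around a 1500 ms rhythm, while the perceptual tasks start after a delay that varies over 2000 ms (1000 to 3000 ms). Fingers rest on the keys, speed is asked for, and there are 300 scored trials per session.

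At stake is the reading of mean flanker RT. If impulsive pressing differs between sessions or groups, part of that difference would appear as a change in flanker speed and accuracy. The flanker RT would also enter the planned correlations cleaned differently at the fast end from the measures it is set against.

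**Working it through.** The plan gives no figure to reproduce here: no formal sample size calculation is made and no anticipation rate is stated. The check is a comparison of the rules, followed by a mixture calculation for size.

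**Rules side by side**

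| Measure | Fast limit | Slow limit | Handling |
|---|---|---|---|
| Flanker | none | 1000 ms | error and excluded |
| RT task, collection | 100 ms | 3 s | trial repeated |
| RT task, analysis | 100 ms | 1500 ms | set to infinity |
| Fishing RT | 100 ms | 1000 ms | discarded |

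The Oral Trail Making Test is a total completion time, so it is not a counterexample.

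**Inputs from the protocol.** There are 20 incongruent and 80 congruent trials in each of 2 blocks, and 100 neutral trials in one block. That is 40 + 160 + 100 = 300 scored trials. Results are obtained per block.

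**Assumed inputs (none is in the documents).** Genuine incongruent RT is 550 ms, shown also for 500 to 700 ms, with genuine accuracy 90%. Anticipations average 50 ms (spread evenly over 0 to 100 ms), half are correct by chance, and they make up a share a of 1% to 5% of trials. The flanker rule is read as dropping listed responses from mean RT while counting them in proportion error. If they were excluded from everything, proportion error would contain no errors.

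**One surviving anticipation.** Shift in a mean of n trials = (50 - genuine RT) / n.

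- Incongruent block, n = 20: (50 - 550)/20 = -25 ms. For genuine RT 500 to 700 ms: -22.5 to -32.5 ms.
- Both blocks pooled, n = 40: -500/40 = -12.5 ms.
- One wrong anticipation adds 1/20 = 5 percentage points to a block's incongruent error.

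**Average bias.**

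Mean RT = [(1 - a) × 0.90 × 550 + a × 0.5 × 50] / [(1 - a) × 0.90 + a × 0.5]

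Error = (1 - a) × 0.10 + a × 0.5

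- a = 1%: (490.05 + 0.25)/0.896 = 547.2 ms, bias -2.8 ms; error 10.4%.
- a = 2%: (485.10 + 0.50)/0.892 = 544.4 ms, bias -5.6 ms; error 10.8%.
- a = 5%: (470.25 + 1.25)/0.880 = 535.8 ms, bias -14.2 ms; error 12.0%.

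Over genuine RT 500 to 700 ms, the bias runs from -2.5 ms (500 ms, 1%) to -18.5 ms (700 ms, 5%).

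**Incongruent-congruent contrast at 5%.** Assume congruent RT 500 ms and accuracy 97%: (0.9215 × 500 + 0.025 × 50)/0.9465 = 488.1 ms, bias -11.9 ms. The contrast moves from 50 ms to 535.8 - 488.1 = 47.7 ms, a shift of about 2 ms.

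**Before-after change.** At the same rate on both occasions and unchanged genuine RT, the biases cancel. If the rate rose from 1% to 5%, the apparent change would be 535.8 - 547.2 = -11.4 ms, with 12.0 - 10.4 = 1.6 points more error.

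**What a 100 ms floor leaves.** If all anticipations lie under 100 ms, the RT bias goes to zero, but only because of that assumption. If they are spread evenly over 0 to 200 ms, half survive with a mean of 150 ms. At 5%, mean RT after the floor is (0.855 × 550 + 0.0125 × 150)/0.8675 = 544.2 ms, a remaining bias of about -6 ms.

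**The case against.** The strongest reply is that a fast cutoff is a data-cleaning detail that an article may leave to its full analysis plan, and that the flanker sentence does not say its list is exhaustive. This stands only in part. The article does fix the flanker rule, including a slow limit, and it states fast limits for the other RT measures. Someone applying the sentence as written would keep a correct press at 40 ms.

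Other objections do limit the point:

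- A reader might infer a single 100 ms rule that the flanker task breaches. The documents do not support that. The comparators are two measures, both simple detection responses, with three ways of handling fast responses and different upper limits. In a two-choice task the accuracy rule already removes about half of blind presses from mean RT, and the double-response rule removes some more.
- A reader might infer that the trial will show a false speed-up after exergaming. The 11 ms figure needs an assumed fivefold rise in anticipations, for which the documents give no basis.
- A reader might infer that inhibition itself is mismeasured. Anticipations affect all trial types, so the contrast between them moves by only about 2 ms in the example. Because RT and proportion error are both obtained, faster but less accurate responding would be visible.
- The planned correlations are exploratory, and the measures already differ at the slow end. A flanker floor would not fully align them.
- Whether a wrong press under 100 ms belongs in proportion error is an analyst's choice. The protocol does not settle it for any accuracy outcome.

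**Conclusion.** The point holds, at minor severity. The flanker rule has a slow limit and no fast one, while the protocol's two other trial-level RT measures treat responses under 100 ms as invalid. As written, correct-key anticipations stay in mean flanker RT. One of them moves a 20-trial incongruent block mean by about 25 ms if genuine RT is about 550 ms. At an assumed 1% to 5% of trials the average bias is about -3 to -14 ms.

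Genuine RT, accuracy, the anticipation rate and the timing of anticipations are all assumptions, and the true rate may be low. The documents do not support a claim that before-after or group comparisons are distorted. That requires a rate that differs between the occasions or groups compared. No feasibility outcome is touched. The flanker is one of several secondary measures in Table 1, in a non-randomised pilot of at least 12 per group whose own limitations section asks for cautious interpretation.

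**What to change.** Add to the Executive Function section of the Statistical Analysis Plan that flanker responses under 100 ms are excluded from mean RT whichever key was pressed, and that their rate is reported by group and session. State in advance whether such responses count in proportion error, or show proportion error both ways. The reported rate would show whether anticipation changes between sessions, which is the condition under which it matters most.

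The cost is a sentence and one filter on trial-level data, with no change to the task, schedule or sample. A few trials per person are lost, and anticipations slower than 100 ms would still remain in mean RT. Setting the limit before the data are analysed avoids a cutoff chosen after seeing them.

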## Methods

### Study Design

This is a 6-week pilot study to examine the feasibility, acceptability, and usefulness of a co-designed VR exergame intervention among older adults as well as the feasibility of the study procedures and assessment protocol. A control group will be used to account for practice and exposure effects and will follow the same protocol as that described for the experimental group without exposure to the exergame; they will read 3 times a week for 15 to 20 minutes instead of engaging with our exergames. To maintain consistency between the control and experimental conditions, the same questionnaires and surveys will be completed by all the participants in both groups, except for the *perceived enjoyment* and *rate of perceived exertion (RPE)* scales, which will be completed only by the experimental group. Both qualitative and quantitative methods will be used to provide pilot data on potential outcomes of interest. Although this study will evaluate the feasibility of both the study intervention and study control arms, we will not randomize the participants. Participants in the intervention arm will be recruited first, followed by a wave of participants recruited to the control group. The study is based in Waterloo but will be carried out remotely, so participants from across Canada will be eligible.

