**Executive function**																					
	OTMT^d^ (A and B)	✓	✓	✓				✓		✓				✓		✓				✓	
	VF^e^	✓	✓	✓				✓		✓				✓		✓				✓	
	Modified flanker task	✓	✓	✓				✓		✓				✓		✓				✓	

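### The flanker analyses adjust for the no-response rate, a result of the same task recorded mostly after exposure starts, so the time and group effects may be biased

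*Protocol article*

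**What the plan says.** The Executive Function paragraph of the Statistical Analysis Plan defines two flanker outcomes: "mean RT and proportion error (1-accuracy) for each block of flanker responses will be obtained and further separated by congruence". It lists three kinds of failed trial, namely wrong responses, responses later than 1000 ms and double responses, and closes the list with "double responses for a single stimulus will be considered as errors and excluded from the analysis". It does not name the analysis from which they are excluded. It then sets the adjustment: "The rate of no response and gender will be included as covariates". No visit is given for the no-response rate.

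Table 2 places the task at baseline, before and after a session in weeks 1, 3 and 5, and at follow-up. The Outcome Analyses section applies repeated-measures and mixed ANOVAs to data of this kind "to understand changes by time (before and after), group (control vs experimental), and day". The Study Design section says "we will not randomize the participants"; the intervention arm is recruited first and the control arm afterwards.

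**The concern.** A covariate in a comparison of groups or times should be something that the exposure cannot have changed. Gender meets that test. The no-response rate does not obviously meet it, because it comes from the same paced task as the outcomes and plausibly reflects the same speed and attention. Taken at a visit after exposure has begun, it may carry part of the effect that the model is meant to estimate. It may also share unmeasured causes with response time, in which case conditioning on it brings in bias even without a causal path. If non-responses lower accuracy, proportion error would in addition be adjusted for one of its own components.

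At stake are the flanker change estimates. The Sample Size section says the pilot should feed the sample size of a larger trial, so a shifted estimate could be carried into that design.

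A second, smaller matter is the unnamed scope of the exclusion rule. The paragraph does not say which outcome loses the failed trials, or how a trial with no response enters accuracy.

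**Working it through.** The plan states no flanker effect, SD or no-response rate, so there is no figure to reproduce. Effect values below are assumptions in SD units.

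**1. Timing (Table 2).** Occasions: 1 baseline + 3 weeks × 2 (before and after) + 1 follow-up = 8. Only baseline and week 1 before the session can precede exposure, so at least 8 − 2 = 6 follow its start.

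**2. General formula.** Let T be the total effect on the outcome, δ the effect on the no-response rate, and β the within-group slope of the outcome on that rate. Then

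adjusted effect = T − δ × β.

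If δ = 0, the adjusted effect equals T. If δ and β are both nonzero, it does not.

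**3. Assumed single-ability model.** Response time and no-response rate have unit variance and load λ₁ and λ₂ on one ability, which the exposure shifts by d. Then T = λ₁d, δ = λ₂d and β = λ₁λ₂, so

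adjusted = λ₁d − λ₂d × λ₁λ₂ = λ₁d(1 − λ₂²).

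The share lost is λ₂²: 0.5² = 25%, 0.6² = 36%, 0.7² = 49%.

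**4. Assumed trade-off between speed and omissions.** If waiting longer means fewer misses, β is negative. With T = −0.5, δ = −0.5 and β = −0.5, adjusted = −0.5 − (−0.5)(−0.5) = −0.75, which is further from null.

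**5. Simulation, 12 per group, 4000 runs per setting.** Direct group effect −0.5; effect on no-response δ; path from no-response to response time b; shared unmeasured cause U with coefficient c. The no-response rate has within-group variance 1, and U enters it with weight √0.5 = 0.707. Hence T = −0.5 + δb, β = b + 0.707c, and adjusted = −0.5 − 0.707δc.

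| δ | b | c | T | Adjusted, formula | Adjusted, simulated |
|---|---|---|---|---|---|
| 0 | 0.5 | 0.5 | −0.50 | −0.50 | −0.51 |
| −0.25 | 0.5 | 0 | −0.625 | −0.50 | −0.51 |
| −0.25 | 0 | 0.5 | −0.50 | −0.41 | −0.42 |
| −0.25 | 0.5 | 0.5 | −0.625 | −0.41 | −0.41 |
| −0.5 | 0.5 | 0 | −0.75 | −0.50 | −0.51 |
| −0.5 | 0 | 0.5 | −0.50 | −0.32 | −0.32 |
| −0.5 | 0.5 | 0.5 | −0.75 | −0.32 | −0.31 |
| −0.8 | 0.5 | 0 | −0.90 | −0.50 | −0.50 |
| −0.8 | 0 | 0.5 | −0.50 | −0.22 | −0.22 |
| −0.8 | 0.5 | 0.5 | −0.90 | −0.22 | −0.21 |

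Without the covariate, the simulated mean was within 0.02 of T in every setting. The sampling SD of one unadjusted estimate was 0.44 to 0.56.

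**6. Error rule.** With the two mixed blocks there are 2 × 20 = 40 incongruent trials. Suppose 6 are errors. Counted, proportion error is 6/40 = 0.15. Removed first, it is 0/34 = 0 for this and every participant. Non-responses leave a further choice: with N trials presented, E errors and O omissions, the outcome could be (E + O)/N, E/N or E/(N − O). The text does not say which.

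**The case against.** **Visit left open.** The plan does not say that a post-exposure value will be used, and the choice of visit could be settled in a fuller analysis plan. This is fair as to timing, which is inferred from Table 2. But the adjustment itself is stated without limit, and an analysis plan that followed the sentence would carry the problem forward.

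**No harm if non-response is unaffected.** This stands. With δ = 0 the adjusted estimate is unbiased and somewhat more precise (sampling SD 0.42 against 0.46 at b = 0.5, c = 0).

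**Data quality.** In unsupervised web testing on uncontrolled equipment, non-response may partly reflect technical trouble. That is a reason to report it, and perhaps to adjust for its baseline value in non-randomized groups. It does not justify conditioning on a value that exposure may have changed.

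Three stronger readings are tempting and are not supported:

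- A reader might infer that excluding errors sets proportion error to zero, so that both outcomes are distorted. Classing trials as errors has a purpose only if they are counted, so the sensible reading is that they leave mean response time alone. A wording clarification remains.
- A reader might infer bias toward no effect. That follows from the single-ability model, and step 4 shows the opposite under another assumption.
- A reader might see a contradiction in treating late responses as errors and missing ones as a covariate. A late response has a time and a missing one has none, so different handling is not in itself an error.

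**Conclusion.** The point holds in a limited form. As written, the flanker models condition on a performance result of the same task, recorded mostly after exposure starts and not limited to baseline. This may bias the time and group effects on mean response time and proportion error, provided that exergaming or reading changes non-response. The document gives nothing from which to set direction or size. In the simulated settings with δ ≠ 0 the gap between total and adjusted effect runs from 0.09 SD (−0.50 against −0.41) to 0.68 SD (−0.90 against −0.22), all on assumed values.

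Severity is minor to moderate. The flanker task is one of three secondary executive-function instruments in a non-randomized pilot with at least 12 per group. No feasibility conclusion depends on it, and the limitations section already urges caution with the statistics. The exclusion rule needs clarification only.

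**What to change.** - Remove the concurrent no-response rate from the flanker covariates, or state that only its baseline value is used. Gender can stay.
- Report the no-response rate as a separate outcome, by group and visit.
- State that incorrect, late and double responses are excluded from mean response time only and are counted as errors in proportion error.
- State whether non-responses count as errors, with all presented trials as the denominator.

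No further covariates are needed for this repair: the before and after ANOVA already contains the baseline flanker score as a level of the outcome, and adding age would be a preference. The cost is analysis wording only. The task already yields the data.
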